### Statistical analysis

The analysis will be by intention to treat, and will be carried out in the following four steps:

#### Step 1: Summarising trial data

Baseline data and outcome data will be summarised separately. For continuous variables (eg age and FSH level), we will examine the distribution of the observations, and if normally distributed we will then summarise them as means with standard deviations (SDs). If they are non-normally distributed, then medians and inter-quartile ranges (IRQs) will be reported. For dichotomous data (eg clinical pregnancy), we will provide proportions (or percentages).

For our main outcome measure (the number of oocytes collected), as the number of oocytes is not a dichotomous or continuous variable but is a count, and as it is more likely not to be normally distributed, a model for count such as the negative binomial model will be used for analysis.

In addition to the baseline and outcome data, we will also summarise the recruitment numbers, those participants lost to follow-up, protocol violations and other relevant data.

#### Step 2: Inter-group comparisons

A test for overall comparison (eg ANOVA, or if assumption for ANOVA are not met, a non-parametric equivalence such as Kruskal-Wallis) will be employed for each outcome across all three interventions (A, B, and C), and if this is found to be significant (at a p-value of ≤ 0.05), then we will proceed to pair-wise comparisons (i.e., A vs B, B vs C, A vs C). We appreciate that multitudes of pair-wise comparisons can suffer from Type I (false-positive) error, and will therefore adjust for multiplicity of comparisons (by using steps such as Bonferroni and Tukey's procedure).

The statistical procedures for pair-wise comparisons will depend on the nature of the data: for example, for dichotomous outcomes, we will use Fishers Exact Test or chi-square as appropriate, and for continuous outcomes we will use t-test if the observations in each trial arm are normally distributed; if non-normally distributed, then Mann-Whitney-U test will be employed. Although p-values will be reported, the focus will be on providing 95% confidence intervals around point estimates as these are more useful in interpreting the findings of the trial.

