### Secondary endpoints

• The total dose of follicle stimulating hormone (FSH) used for ovarian stimulation

• The number of mature eggs retrieved

• The number of embryos available for transfer

• The clinical pregnancy rate and

• The embryo implantation rate

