#### Step 4: Adjustments and sensitivity analyses

If randomisation fails to achieve balanced groups, then we will perform secondary analyses in which we will adjust for unbalanced prognostic factors using procedures such as logistic regression. If the primary unadjusted analysis and secondary adjusted analysis are at discordance, then we will give greater weighting to the primary analysis in the interpretation of trial findings.

For issues such losses to follow-up, missing data, and protocol violations, we will attempt sensitivity analyses to explore the effect of these factors on the trial findings. As a secondary analysis, we will adjust for missing data using imputation techniques to explore the effects of such imputations on the trial findings.

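### The embryo implantation rate has no stated unit or denominator, and the tests named for dichotomous outcomes would ignore several embryos per woman if it is counted per embryo

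*Protocol article*

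**What the plan says.** Under Secondary endpoints, the article lists "The embryo implantation rate" as an item separate from the clinical pregnancy rate. It gives no numerator, denominator or unit of analysis. The Randomisation and Methods sections make the woman the unit of randomisation. The Embryo transfer section speaks of embryos in the plural and lets their number and quality decide the day of transfer, so more than one embryo per woman is contemplated.

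Step 2 chooses pairwise tests by type of data and says, by way of example: "for dichotomous outcomes, we will use Fishers Exact Test or chi-square as appropriate". Continuous outcomes get a t-test or Mann-Whitney test. The overall three-arm test for each outcome is ANOVA or Kruskal-Wallis, also given as an example. Pairwise tests follow only if the overall test is significant, and are then adjusted by steps such as Bonferroni or Tukey.

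Step 4 adds that, if the groups turn out unbalanced, "we will adjust for unbalanced prognostic factors using procedures such as logistic regression". That analysis is secondary and names no clustering term. On the population, the Statistical analysis section states: "The analysis will be by intention to treat". No section mentions several embryos from one woman.

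**The concern.** An embryo either implants or does not, and a rate named after embryos and listed apart from pregnancy reads most naturally as a proportion of embryos. Under the Step 2 rule, the route for such an outcome is chi-square or Fisher's exact test. Embryos placed in one uterus share maternal factors, so their outcomes are likely to be correlated. Treating them as independent understates the variance. Step 2 says that the emphasis will lie on 95% confidence intervals, and these are what would be too narrow.

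The denominator raises a second issue. A rate per embryo transferred does not exist for a woman who has no transfer. The Background says that poor responders often have their cycle cancelled, and HCG is given only once at least three follicles reach 17 mm, so such women are to be expected. The regimens are compared on ovarian response, so reaching transfer is a post-randomisation event that they may affect. A comparison restricted to transfers is then no longer a comparison of the groups as randomised.

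**Working it through.** **The plan's own figure.** The article states no figure for implantation. Its only calculation concerns oocytes: 2 × (1.960 + 1.282)² × (2.5/2)² = 32.8, or 33 per arm by the normal approximation. The t-distribution gives 33.8, hence the stated 34 per arm and 102 in total. It reproduces, but does not bear on this endpoint.

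**Inputs**
- From the article: 34 women per arm; alpha 5%, taken as two-sided; three pairwise comparisons.
- Assumed, because the article does not give them: m = 2 embryos per woman with a transfer; within-woman correlation (ICC) 0.05 to 0.5.

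**Formulas**
- Design effect: DE = 1 + (m − 1) × ICC.
- True type I error of an unadjusted two-sided 5% pairwise test: 2 × Φ(−1.96/√DE).
- The same under Bonferroni, with nominal level 0.05/3 = 1.67% and critical value 2.394: 2 × Φ(−2.394/√DE).
- Shortfall in interval width: 1 − 1/√DE.

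**Results for m = 2**

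| ICC | DE | Unadjusted (nominal 5%) | Bonferroni (nominal 1.67%) | Interval too narrow by |
|---|---|---|---|---|
| 0 | 1.00 | 5.0% | 1.67% | 0% |
| 0.05 | 1.05 | 5.6% | 1.95% | 2% |
| 0.1 | 1.10 | 6.2% | 2.25% | 5% |
| 0.2 | 1.20 | 7.4% | 2.89% | 9% |
| 0.5 | 1.50 | 11.0% | 5.06% | 18% |

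**Sensitivity to m.** Over ICC 0.05 to 0.5, the unadjusted error runs from 5.3% to 8.0% at a mean of 1.5 embryos, and from 5.9% to 13.8% at 2.5. With one embryo per woman, DE = 1 and nothing is lost.

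**Simulation check.** Beta-binomial data were generated with no treatment effect, assuming 34 women per arm, 70% with a transfer, one to three embryos (mean 1.9) and 15% implantation. That gives 34 × 0.7 × 1.9 = 45 embryos per arm. Pairwise embryo-level chi-square rejected in 5.1% (ICC 0), 5.8% (0.05), 6.1% (0.1), 7.7% (0.2) and 11.9% (0.5), in line with the formula.

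**Denominator.** No arithmetic is possible without a transfer rate by arm, so the possible readings are set side by side:
- Implantations over all embryos transferred: women without a transfer contribute nothing, and embryos are clustered.
- A proportion per woman, compared by Mann-Whitney: the clustering is gone, but for a woman without a transfer the proportion is 0/0 and she still drops out.
- Implantations per woman randomised, zero if no transfer: every woman counts, and the observations are independent. Only this reading meets the intention-to-treat statement without further qualification.

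**The case against.** The strongest reply is that the article never says it will run a chi-square on embryos. The Step 2 list is introduced as an example. The only dichotomous outcome that Step 1 names is clinical pregnancy, which is a woman-level outcome. A per-woman proportion tested by Mann-Whitney would fit the text equally well. A condensed article may also leave the definition of one secondary endpoint to the full protocol or SAP.

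Much of this stands, and it rules out several stronger readings that a reader might infer:
- That chi-square and Fisher's exact test are the only tests planned. They are examples, and logistic regression is named too, although only for secondary adjustment after imbalance and without allowance for clustering.
- That the plan leaves out women without a transfer. Neither test excludes anyone. A denominator would do so, and none is stated.
- That 7.4–11% is the plan's own error rate. It ignores the overall test that must first be significant, as well as the Bonferroni or Tukey step, and it takes the upper part of the ICC range.
- That a three-arm chi-square is planned. The overall test named is ANOVA or Kruskal-Wallis.
- That an arm losing its worst patients before transfer would look better. The article calls the evidence on these regimens inconclusive or inconsistent, and the bias could run either way.

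The reply does not remove the point. Step 1 recognises that oocyte number does not fit the default tests and names a negative binomial model for it. No such exception is made for the one endpoint whose natural unit differs from the unit of randomisation. The stated rule, followed on its most natural reading, therefore misfits a listed endpoint. The alternative per-woman proportion still has no value for women without a transfer.

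**Conclusion.** The concern holds in conditional form and is minor. The unit and denominator of the implantation rate are not stated. If it is counted per embryo, the tests named for dichotomous outcomes give intervals that are too narrow: by about 2–5% in width for ICC 0.05–0.1 and 9–18% for ICC 0.2–0.5, at two embryos per woman. The inflation of type I error is modest at the lower correlations and material only at the higher ones. Under Bonferroni the relative inflation persists, and the overall-test gate can only lower the chance of a false pairwise claim from there. All of this rests on assumed embryo numbers and correlations.

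If the denominator is embryos transferred, the comparison also conditions on a post-randomisation event, contrary to the intention-to-treat statement, with a bias of unknown size and direction. One secondary endpoint is affected. The primary analysis of oocytes retrieved and the sample size are not.

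**What to change.** State the unit and denominator of the implantation rate. Make the main analysis the number of implantations per woman randomised, with zero for a woman who has no transfer. This keeps the woman as the unit and every randomised woman in the comparison.

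If a rate per embryo transferred is also reported, analyse it by logistic regression using GEE or cluster-robust standard errors, with woman as the cluster, and label it as conditional on transfer.

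The cost is a sentence or two of analysis wording and slightly wider intervals for the per-embryo rate. No additional data or participants are needed.

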### Trial statistics

#### Number of participants

Sample size calculation was based on the observed differences in eggs collected from existing literature as well as on the judgement on what constitutes as a clinically Minimally Important Difference (MID), which was judged to be increasing the number of oocytes retrieved from 3 to 5. For this difference of 2 oocytes retrieved, with a standard deviation of 2.5 (as observed in the existing literature), for a power of 90% and an alpha of 5%, 102 women in total will need to be recruited (34 each of the three arms of the trial).

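### Step 2 corrects for multiplicity twice: with three arms the global test at 0.05 already protects the pair-wise tests, so the added Bonferroni or Tukey step only costs power

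*Protocol article*

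**What the plan says.** All the analysis text is in the Protocol article, Statistical analysis, Step 2: Inter-group comparisons. Each outcome first gets an overall test across the three regimens, and "if this is found to be significant (at a p-value of ≤ 0.05), then we will proceed to pair-wise comparisons". The pairs are all three possible ones ("i.e., A vs B, B vs C, A vs C"). The authors acknowledge the false-positive risk of several pair-wise comparisons and "will therefore adjust for multiplicity of comparisons (by using steps such as Bonferroni and Tukey's procedure"). The following paragraph says p-values will be reported but "the focus will be on providing 95% confidence intervals around point estimates".

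Trial statistics, Number of participants, plans for "increasing the number of oocytes retrieved from 3 to 5", "with a standard deviation of 2.5 (as observed in the existing literature"), 90% power and an alpha of 5%, and concludes that "102 women in total will need to be recruited (34 each of the three arms of the trial").

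**The concern.** The gate and the added adjustment are both explicit, and both exist to control false positives among the same three pairs. For three groups the gate alone is enough. The second layer therefore lowers the chance of detecting a true difference and protects against nothing further at the 5% family-wise level. This matters because the stated objective is to find which of the three regimens is most effective, and only the pair-wise results can answer that. The stated power also belongs to a more lenient test than the one Step 2 would apply.

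A second, smaller point is the level of the intervals. The plan ranks them above the p-values but does not say whether 95% is the level of each interval or of the set of three. If it is the level of each, interval and adjusted p-value can point in different directions for the same pair.

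**Working it through.** **Inputs.** From Number of participants: difference 2, SD 2.5, 34 per arm, alpha 5%, power 90%. From Step 2: gate at p ≤ 0.05, three pairs, Bonferroni or Tukey. My assumptions: two-sided alpha (sidedness is not stated), a normal model, and a pooled SD on 3 × 34 − 3 = 99 degrees of freedom.

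**1. The plan's own figure.** For a two-sample t-test at two-sided 5%, power is 89.3% at 33 per arm and 90.15% at 34. So 34 per arm, and 3 × 34 = 102, reproduce. (The normal approximation gives 33.) At a Bonferroni level of 0.05/3 = 0.0167 the normal approximation needs 43 per arm, or 129 in total. The stated size is therefore that of one unadjusted pair at 5%.

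**2. Why the gate suffices with three arms.** There are three possible truths.
- All three arms are equal. A false pair-wise claim then requires the gate to be passed, which happens with probability 5%.
- Exactly one pair is equal. Only one true null hypothesis remains, and it is tested at 5%.
- No pair is equal. No false claim of a difference can be made.

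Two pairs cannot be equal without the third being equal too, so the list is complete. The family-wise error is at most 5% in every case. In simulation it is 5.0% when all arms are equal and 4.9% to 5.1% for the equal pair at means 5/3/3. With negative binomial counts, Kruskal-Wallis as gate and Mann-Whitney for pairs, the two figures are 4.8% and 4.6%.

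**3. What the second correction costs.** The standard error of a difference is 2.5 × √(2/34) = 0.606 eggs. Critical values on 99 df are 1.984 (unadjusted), 2.435 (Bonferroni) and 2.379 (Tukey, the studentized range value divided by √2). Simulated power at means 5/3/3, with an F-test gate:

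| Procedure | One given true pair | Best arm beats both others |
|---|---|---|
| Gate, then 5% tests | 88% | 84% |
| Gate plus Bonferroni | 80% | 70% |
| Gate plus Tukey | 82% | 72% |

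Repeated runs move the last column by up to about one point (69% to 70% for Bonferroni, 71% to 72% for Tukey). Without any gate or adjustment, one pair has 90.4% power on 99 df. The gate itself therefore costs about 2 points, and the added adjustment a further 6 to 8 (88 − 82 and 88 − 80).

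**4. The interval question.** Half-widths of a pair-wise interval:
- individual 95%: 1.984 × 0.606 = 1.20 eggs
- Bonferroni: 2.435 × 0.606 = 1.48 eggs
- Tukey simultaneous: 2.379 × 0.606 = 1.44 eggs

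If the emphasised intervals are individual, an observed difference between 1.20 and 1.48 eggs (Bonferroni) or 1.20 and 1.44 eggs (Tukey) gives an interval that excludes zero beside a non-significant adjusted p-value. In terms of the unadjusted p-value, the zone runs from 0.017 or 0.019 up to 0.05. For example, a difference of 1.3 eggs has the interval 1.3 ± 1.20, or 0.10 to 2.50, an unadjusted p of about 0.035 and a Bonferroni p of about 0.10. Over all trials, at least one pair lands in the zone after a significant gate in about 17% (Bonferroni) or 15% (Tukey) at means 5/3/3, and in about 28% or 25% at 5/4/3. If intervals and p-values come from the same procedure, the zone is empty.

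**The case against.** The strongest reply is that a further adjustment after a gate is conservative but valid: it breaks no error guarantee and contradicts nothing in the document. That is true, and the point is not that the planned tests are wrong. It is that they give up power without need, below the figure used to justify the sample size.

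A reader might go further and infer that the plan contradicts itself by adjusting only the p-values and then featuring unadjusted intervals. The text does not support this. It promises adjustment of comparisons, not of p-values alone, and it never calls the intervals unadjusted. Tukey's procedure, one of the two named, yields simultaneous 95% intervals that agree with its p-values. Whether intervals are individual or simultaneous is also the kind of detail a condensed article may leave to an analysis plan that is not shown. Alone, the interval question would be no more than a request for clarification. A reader might likewise quote the roughly 12% chance, with no true differences, that at least one of three individual 95% intervals excludes zero. That applies only if intervals are read without the gate; after the gate it is 5%.

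One further reservation stands. Step 1 plans a count model, such as the negative binomial, for the primary outcome, so the figures in eggs are a guide. The closed-testing argument does not depend on normality, provided each test is valid at 5%. The ratios of critical values (2.435/1.984 = 1.23 and 2.379/1.984 = 1.20) should be similar.

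**Conclusion.** The point holds as a matter of efficiency, not validity. Step 2 explicitly stacks two multiplicity corrections where, with three arms, the first is sufficient. At the planning values the second costs about 6 to 8 percentage points of power for one true 2-egg difference and about 12 to 14 points for showing that the best arm beats both others (84 − 72 and 84 − 70). The 90% in the sample-size section is the power of a single unadjusted 5% comparison. The sample size is correctly computed for that test, but Step 2 as written delivers 80% to 82% per pair. These figures rest on a normal model, SD 2.5, 34 evaluable women per arm, two-sided 5% tests and means 5/3/3. The mismatch between interval and p-value is conditional: it arises only if the 95% intervals are individual ones, which the document leaves open.

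**What to change.** In Step 2, keep the global test at 0.05 and delete the additional Bonferroni or Tukey adjustment. State that with three arms the gate followed by pair-wise two-sided 0.05 tests is a closed procedure, and that pair-wise significance is claimed only after a significant global test. Label the 95% intervals as individual. In Number of participants, restate the per-pair power as about 88% at the planning values.

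This takes a few sentences and no extra patients or data, and the family-wise error stays at 5%. The small downside is that three individual 95% intervals have joint coverage of about 88%, hence the label. An individual interval can also exclude zero when the global test is not significant (about 4% of trials at 5/3/3 and 8% at 5/4/3), hence the rule on when significance may be claimed.

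If simultaneous intervals are preferred, drop the gate and use one simultaneous procedure for both p-values and intervals. With Tukey the intervals widen by about 20% (half-width 1.44 instead of 1.20 eggs) and per-pair power is about 82%.

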#### Step 3: Sub-group analysis

We will give emphasis to planned (a priori) sub-groups in our analyses. However, we are aware sub-groups analysis can suffer from false positive (due to multiplicity of comparisons) and false negative (due to reduced sample sizes) results, and will place limited importance in subgroup findings in relation to the overall (global) findings. We will use post-hoc subgroup analysis only for the purpose of hypothesis generation.

#### Step 4: Adjustments and sensitivity analyses

If randomisation fails to achieve balanced groups, then we will perform secondary analyses in which we will adjust for unbalanced prognostic factors using procedures such as logistic regression. If the primary unadjusted analysis and secondary adjusted analysis are at discordance, then we will give greater weighting to the primary analysis in the interpretation of trial findings.

For issues such losses to follow-up, missing data, and protocol violations, we will attempt sensitivity analyses to explore the effect of these factors on the trial findings. As a secondary analysis, we will adjust for missing data using imputation techniques to explore the effects of such imputations on the trial findings.

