### Primary endpoints

• Number of eggs retrieved per IVF treatment cycle started.

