### Randomisation

Third party, distant, internet-based block randomisation with minimisation will be used to ensure randomisation and complete allocation concealment. The aim of minimisation would be to balance for the following prognostic variables (age, body mass index, previous pregnancies and previous live birth). Women may be randomised into the study by internet randomisation [12] or by telephoning a central office.

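### The primary analysis ignores the four factors used for minimisation, so if they are prognostic its intervals are too wide and its 5% test is conservative

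*Protocol article*

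**What the plan says.** Allocation (Randomisation): "Third party, distant, internet-based block randomisation with minimisation will be used to ensure randomisation and complete allocation concealment". The purpose is stated next: "The aim of minimisation would be to balance for the following prognostic variables (age, body mass index, previous pregnancies and previous live birth").

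Primary endpoint (Primary endpoints): "Number of eggs retrieved per IVF treatment cycle started".

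Analysis of that endpoint:
- Step 1: "a model for count such as the negative binomial model will be used for analysis". No covariates are named.
- Step 2: "A test for overall comparison (eg ANOVA, or if assumption for ANOVA are not met, a non-parametric equivalence such as Kruskal-Wallis"), followed, if p ≤ 0.05, by pairwise tests with a multiplicity adjustment. None of the tests named carries covariates.
- Step 4: "If randomisation fails to achieve balanced groups, then we will perform secondary analyses in which we will adjust for unbalanced prognostic factors". The section calls the primary analysis unadjusted and says that, if primary and adjusted results are discordant, "then we will give greater weighting to the primary analysis in the interpretation of trial findings".

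**The concern.** Minimisation reduces the chance differences between arms in the factors it balances. If those factors predict oocyte number, the treatment comparison becomes more precise than under simple randomisation. An analysis that leaves them out cannot see this gain: the variance they explain stays in the residual term, so the reported standard error exceeds the true one.

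The trigger in Step 4 does not repair this. Adjustment depends on observed imbalance, which minimisation is meant to prevent for these four factors. The factors that belong in the model because of the design are therefore those least likely to enter it.

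Two features of Step 2 make this matter. Pairwise comparisons proceed only if the overall test is significant, so a conservative overall test can hold back every comparison of interest. The protocol also says that interpretation will focus on 95% confidence intervals, and these are what become too wide. There are only 34 women per arm.

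**Working it through.** **Inputs from the protocol (Number of participants):** difference 2 oocytes (3 to 5), SD 2.5, power 90%, alpha 5% (two-sided assumed), 34 per arm, 102 in total.

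**The plan's own figure.** A two-sample t-test calculation gives exactly 34 per arm (power 90.2%), hence 102. The normal approximation gives 33 per arm. The sample size reproduces and is not in question.

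**Assumption.** R², the share of variance in oocyte number jointly explained by the four factors, is not in the protocol. I use 0.05, 0.10 and 0.20, with 0 as reference, on the linear scale of the sample-size calculation and with balance taken as complete.

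**Formulas** (normal approximation throughout, so that both analyses are compared on one basis):
- Reported unadjusted SE of a pairwise difference: 2.5 × √(2/34) = 0.606, so difference/SE = 2/0.606 = 3.298.
- True SE under balance = 0.606 × k, where k = √(1 − R²) = 0.975, 0.949, 0.894.
- True type I error of the unadjusted test: 2 × [1 − Φ(1.96/k)].
- Excess interval width: 1/k − 1.
- Power, unadjusted: Φ[(3.298 − z)/k]. The critical value uses the reported SE, while the estimate varies with the true SE.
- Power, adjusted: Φ(3.298/k − z).
- z = 1.960 at 5% and 2.394 at 0.05/3 = 0.0167 (Bonferroni, three pairs).

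| Assumed R² | True type I error, unadjusted | Excess width | Power at 5%, unadjusted → adjusted | Power at 0.0167, unadjusted → adjusted |
|---|---|---|---|---|
| 0 | 5.0% | 0% | 91.0% → 91.0% | 81.7% → 81.7% |
| 0.05 | 4.4% | 3% | 91.5% → 92.3% | 82.3% → 83.9% |
| 0.10 | 3.9% | 5% | 92.1% → 93.5% | 83.0% → 86.1% |
| 0.20 | 2.8% | 12% | 93.3% → 95.8% | 84.4% → 90.2% |

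Worked row, R² = 0.10: 1.96/0.949 = 2.066, two-sided tail 3.9%; (3.298 − 1.960)/0.949 = 1.411, Φ = 92.1%; 3.298/0.949 − 1.960 = 1.517, Φ = 93.5%.

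**Check by simulation.** Three-arm minimisation of 102 women on four binary factors, 3,000 runs, normal outcomes. The factor prevalences and the 80% biased coin are assumptions. Type I error of the overall test at nominal 5%:

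| Assumed R² | Unadjusted ANOVA | Kruskal-Wallis | Linear model with the four factors |
|---|---|---|---|
| 0 | 4.5% | 4.6% | 4.6% |
| 0.05 | 4.3% | 4.3% | 4.9% |
| 0.10 | 3.4% | 2.8% | 4.3% |
| 0.20 | 2.7% | 2.9% | 5.1% |

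Monte Carlo error is about √(0.05 × 0.95/3000) = 0.4 points. With one arm shifted by 2 oocytes, power of the overall test, ANOVA against the adjusted model, was 92.8% against 93.4%, 93.2% against 94.7%, and 94.5% against 97.1% for R² of 0.05, 0.10 and 0.20. Imperfect balance and the degrees of freedom spent on covariates, both included here, do not change the picture.

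**The case against.** The strongest reply is that the loss is modest and of unknown size. Minimisation already delivers the lower true variance, so the unadjusted test gains some power too. Comparing adjusted power with the plain 90% design figure, or describing adjustment as equivalent to recruiting more women per arm, would overstate the benefit. The population is restricted to poor responders aged 40 or under, so a low R² cannot be excluded; at 0.05 the gain at 5% is under one point. All of this stands, and the table allows for it.

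Step 4 also speaks of unbalanced prognostic factors in general, which may include factors not minimised on, such as FSH level. So the argument that the trigger will rarely fire covers the four minimisation factors only. That stands as well.

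Three stronger readings are tempting, but the protocol does not support them:
- A reader might infer an inflated false-positive rate. The error runs the other way.
- A reader might see a data-driven choice of primary result. Step 4 fixes the unadjusted analysis as primary in advance and ranks it first, which closes that route.
- A reader might conclude that oocyte number will be analysed by logistic regression. Step 4 names that method only as an example, in a section tied to no single outcome. It suits clinical pregnancy, and Step 1 names a count model for oocytes. Nothing says the count will be dichotomised.

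A last reply is that a separate analysis plan may settle covariates. It could not make the primary analysis adjusted without contradicting Step 4, so this is a matter of what the protocol states.

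**Conclusion.** The point holds as a mismatch between design and analysis that costs efficiency. If the four factors are prognostic, as the protocol says, the primary intervals are too wide and the primary test is conservative. For assumed R² from 0.05 to 0.20, true type I error runs from about 4.4% to 2.8% and excess interval width from about 3% to 12%. Adjustment is worth about 0.8 to 2.5 points of pairwise power at 5% and 1.6 to 5.8 points at the Bonferroni level. If R² is 0 nothing material is lost.

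These sizes rest on the assumed R², near-complete balance and a linear-scale approximation; the negative binomial model itself was not simulated. The flaw does not threaten the trial's validity, but it is worth correcting because the correction is nearly free.

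**What to change.** Amend Steps 2 and 4:
- Make the primary analysis a count model, for example the negative binomial already named in Step 1, containing treatment and the four minimisation factors, with age and body mass index continuous, whatever the observed balance.
- Take the overall test and the multiplicity-adjusted pairwise comparisons, with their confidence intervals, from that model.
- Report the unadjusted result as a sensitivity analysis.
- Delete the imbalance trigger for these four factors and the rule that favours the unadjusted analysis.

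Do not add the previous cycle's oocyte count as a required covariate. The Inclusion Criteria let a woman qualify on follicle numbers alone, so that count may not exist for everyone.

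The cost is wording. All four factors are needed for minimisation, so no new data are required and the sample size need not change.
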